## Abstract

**Background:**

Common low back pain represents a major public health problem in terms of its direct cost to health care and its socio-economic repercussions. Ten percent of individuals who suffer from low back pain evolve toward a chronic case and as such are responsible for 75 to 80% of the direct cost of low back pain. It is therefore imperative to highlight the predictive factors of low back pain chronification in order to lighten the economic burden of low back pain-related invalidity. Despite being particularly affected by low back pain, Hospices Civils de Lyon (HCL) personnel have never been offered a specific, tailor-made treatment plan. The PRESLO study (with PRESLO referring to Secondary Low Back Pain Prevention, or in French, PREvention Secondaire de la LOmbalgie), proposed by HCL occupational health services and the Centre Médico-Chirurgical et de Réadaptation des Massues – Croix Rouge Française, is a randomized trial that aims to evaluate the feasibility and efficiency of a global secondary low back pain prevention program for the low back pain sufferers among HCL hospital personnel, a population at risk for recurrence and chronification. This program, which is based on the concept of physical retraining, employs a multidisciplinary approach uniting physical activity, cognitive education about low back pain and lumbopelvic morphotype analysis. No study targeting populations at risk for low back pain chronification has as yet evaluated the efficiency of lighter secondary prevention programs.

**Methods/Design:**

This study is a two-arm parallel randomized controlled trial proposed to all low back pain sufferers among HCL workers, included between October 2008 and July 2011 and followed over two years. The personnel following their usual treatment (control group) and those following the global prevention program in addition to their usual treatment (intervention group) are compared in terms of low back pain recurrence and the impairments measured at the beginning and the end of the study. The global prevention program is composed of a two-hour information session about low back pain and pain pathways, followed by five weekly 90-min exercise sessions with one physiotherapist per group of eight to ten personnel. A booklet for home use with patient-managed exercise instructions and information (The Back Book) is given to each participant at the end of the program.

An X-ray assessment of the entire spinal column of each participant (in both the control and intervention groups) is performed at the onset of the study in order to analyze sagittal spinopelvic balance as well as lombopelvic morphotype.

**Discussion:**

The results of this study, which is innovative and unique in France, will be available in 2014 and will make it possible to draw conclusions regarding the program’s impact on the risk of recurrence and chronification of low back pain.

**Trial registration:**

http://www.clinicaltrials.gov # NCT00782925

## Background

The estimated annual prevalence of low back pain is between 35 and 50% in France. As the third most important cause of chronic disability, low back pain is the chronic pathology that most often leads to activity limitations in persons aged 45 through 65 years old. Acute low back pain is a benign condition that heals within a few weeks in 90% of cases. That said, between 20 and 44% of patients undergo a recurrence within one year, and 5 to 10% of patients develop chronic low back pain, which in turn is responsible for 70 to 80% of the total cost of low back pain.

Hospital personnel are particularly affected by low back pain. At the Hospices Civils de Lyon (HCL), sick leave related to back problems represents the most important cause of work interruption.

The main risk factor for recurrence or chronification of low back pain is, however, a previous history of low back pain, which encompasses the concepts of severity, pain, duration and functional incapacity. It is therefore of utmost importance to provide treatment that is specifically targeted to these high-risk populations.

No specific medical care strategy has been implemented for these high-risk populations within hospital services. Training sessions focusing on the handling of patients and loads are currently offered to HCL personnel whether or not they suffer from low back pain. These training sessions are very general in nature and can be likened to a primary prevention strategy inspired by back schools. The efficiency of such training in terms of primary prevention has not been demonstrated. On the other hand, these sessions are offered to a population that already presents a history of low back pain, which is the main risk factor for recurrence and chronification.

Multidisciplinary physical retraining programs appeared in the 1980s. As opposed to back schools, these programs approach low back pain along its medico-psycho-social dimensions and take into account its multi-factorial origin. For dealing with chronic severe low back pain that has resisted conventional treatment, such programs are effective, especially in terms of returns to work. Due to their ponderous and expensive nature, however, these programs are reserved for chronic low back pain sufferers. Other programs based on physical retraining programs have since been developed. These lighter programs are now recommended to help prevent the chronification of less severe forms of low back pain.

PRESLO is a study proposed by the HCL occupational health service and the Centre Médico-Chirurgical et de Réadaptation des Massues – Croix Rouge Française that aims to evaluate the effectiveness of a global secondary low back pain prevention program for the HCL personnel who suffer from low back pain. Through its approach that takes into account the biomedical, environmental and psycho-behavioral factors of low back pain, this study provides a unique perspective.

This program, inspired by the concept of physical retraining, is based not only on an overall evaluation of physical, emotional and social dimensions, with for the biomedical angle the novel addition of a lumbopelvic morphotype analysis; but also on a multidisciplinary approach and care plan combining physical activity (training program followed by a home-based program) as well as cognitive learning on the topics of low back pain, pain pathways and the factors favoring the development of chronic low back pain.

## Method

### Objectives

#### Primary objective

To evaluate the effectiveness of a global secondary prevention program for acute or sub-acute low back pain in decreasing the recurrence of low back pain among health care professionals working in health care facilities.

#### Secondary objectives

The secondary objectives are: to evaluate the effectiveness of a global secondary prevention program for acute or sub-acute low back pain on the average time to recurrence of low back pain, and in decreasing the chronification of low back pain among professionals working in health care facilities; to identify risk factors for recurrence of low back pain (personal factors, psychosocial factors, sagittal spinopelvic balance); and, finally, to evaluate the feasibility of the global secondary back pain prevention program *via* the assessment of patient compliance to the program, the assessment of the program by the patients, and the evaluation of the operational model of the program by the patients and the health care professionals involved (physiotherapists and occupational health physicians).

### Study design

The study design as presented in Figure
1 is a two-arm parallel multicenter randomized controlled trial (usual treatment followed on the initiative of each participant versus treatment through the global prevention program).

**Figure 1 F1:**
[figure not shown]
Organizational structure of the PRESLO study (OHP = Occupational Health Physician, PT = Physiotherapist, PRM = Physical and Rehabilitation Medicine Physician).

### Participants and recruitment

The participating professionals were enrolled in the study by the occupational health physicians of the ten HCL hospital facilities involved, either during annual checkups or in the context of a spontaneous and voluntary process on the part of the professionals. Communication campaigns were regularly carried out in order to encourage inclusions (through an article in the HCL electronic newsletter, an information notice accompanying the salary statements of HCL professionals, and an article in the HCL’s specialized journals).

Inclusion and exclusion criteria

Inclusion Criteria

Were include the persons presenting all the following criteria:

Any member of HCL personnel regardless of occupation,

And presenting, over the past three years, one or more episodes of low back pain of less than three months’ duration, whether or not a work interruption was generated (low back pain, lumbo-sciatica or acute or sub-acute cruralgia are considered),

And consenting to participate in the study).

Exclusion Criteria

The persons presenting at least one of the following criteria were excluded:

Previous history of operated vertebral column fractures,

Previous history of discal hernia surgery in two or more locations,

Previous history of lumbar or lumbosacral arthrodesis in three or more locations,

Clinical presentation of radiculalgia with sequelary motor deficiencies or pure radiculalgia with positive Lasègue test (< 60°),

Indication for treatment in a functional restoration program for the vertebral column (that is, group III low back pain sufferers with permanent underlying pain for more than 3 months),

Current painful episode of acute lumbago,

Presence of psychiatric and/or behavioral disorders that decrease the reliability of evaluations,

Unstable cardiac pathology,

Insufficient mastery of the French language,

Pregnant woman.

### Randomization

Following the inclusion visit, the study group of the participants was decided by random allocation. The randomization was stratified and balanced by blocks between the participating occupational health services. The randomization lists were computed using SAS® statistical analysis software (Version 9.1, SAS Institute Inc., Cary, NC).

Each participant was informed by mail of his assignment to a study group following an entry checkup performed by a physiotherapist. In this letter, the study group was identified and, where appropriate, the timetable for the five global prevention program sessions was included. In order to ensure the objectivity of the evaluations, the occupational health physicians were not informed as to which study group each participant was assigned (single blind). At the time of enrollment, participants were also asked not to reveal their study group to the occupational health physician.

### Intervention

#### Intervention group: global prevention program

The global prevention program procedure is presented in Figure
2. This program requires approximately two months and is based on the management of low back pain on both the cognitive level (information about pain pathways and the factors favoring the development of chronification) and the physical level (implementation of an education and training program followed by a home-based program).

**Figure 2 F2:**
[figure not shown]
Procedure and content of the 6 sessions of the PRESLO global prevention program.

##### Education program

This low back pain information program is carried out at the start of the global program. It deals with the factors favoring chronification (including professional factors), the dedramatization of low back pain using anatomical explanations, pain pathways and the impact of emotional factors.

This roughly two-hour information session is led by a physician specialized in functional rehabilitation from the Centre Médico-Chirurgical et de Réadaptation des Massues – Croix Rouge Française, for a group of eight persons.

A copy of the information booklet entitled “Guide du dos,” the French version of The Back Book, is given to each participant at the end of the session as a source of complementary information. This booklet contains simple, reassuring advice about acute low back pain, in seven key messages. It has been demonstrated that the distribution of The Back Book decreases by 25% the number of patients suffering from persistent pain three months after an episode of acute low back pain
[1]. Considering the validation and the impact of the messages disseminated in this booklet
[2],
[3] it appears relevant to use this information source in the context of the PRESLO study.

##### Training program

The training program involves five weekly sessions of 90 min each. The sessions are led by a physiotherapist from the Centre Médico-Chirurgical et de Réadaptation des Massues – Croix Rouge Française, in a rotating manner in order to limit the therapist effect. The patients meet in a group of eight to ten persons.

Each rehabilitation session is composed of three parts: first, a warm-up (15 min) with rhythmic exercises and changes in rhythm (walking forward, backward, on tiptoe, on heels, and so on); second, a period for stretching and mobilizing the rachis (60 min) including relaxation of the lumbar rachis and stretching of the hamstrings, gluteals, quadriceps, psoas and adductors, as well as pelvic tilt awareness exercises; and finally, a third part involving respiratory and postural work (15 min).

The program was conceived in a spirit of continuity and progression from one session to the next. A patient is therefore not allowed to pursue the program in case of absence (except for session 3 or session 4, which are very similar to each other, so one of these sessions can be substituted for the other).

The aims of the training program are: 1) to improve the patient’s knowledge and management of his back through practical education and theoretical explanations; 2) to lessen motor inhibition and the fear of movement through the use of simple, repeated exercises, in the aim of leading the participants toward awareness of their avoidance behavior and encouraging them to resume physical activity; 3) to reinforce global postural control and proprioceptive control; and 4) to raise awareness of factors that can modulate pain.

The physiotherapist emphasizes the purpose of each exercise and also suggests personalized exercises. The aim is to explain techniques and assist participants in their practical acquisition, so that the participants can learn to know and maintain their back.

The training sessions are carried out on the workplace site of the participants in a room that is appropriate for floor exercises.

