### Analysis

Data analysis will be carried out with SAS® statistical analysis software (Version 9.2, SAS Institute Inc., Cary, USA). Results will be expressed with their 95% confidence intervals. All statistical tests were two sided p-value less than 0.05 regarded as significant. An intention-to-treat analysis will first be performed on all of the participants. This analysis may be supplemented with a per-protocol analysis involving the participants for whom the follow-up adhered to the protocol, therefore excluding all deviations from the protocol (see above Table
1).

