### Number of subjects required

With a recurrence rate estimated at 45% for the general population, in order to observe a 25% reduction in recurrence rate that is attributable to the global secondary prevention program, 310 participants per group (a total of 620 participants) are required to achieve at 80% power with Type 1 error rate of 5%.

A 5% increase in the number of participants is planned in order to take into account those lost to follow-up who do not attend all appointments, as well as any early dropouts. The total number of subjects is therefore set at 650.

These 650 professionals were recruited from within ten occupational health services belonging to the participating hospital facilities.

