### Analysis of the secondary outcomes

The effectiveness of the global program on the average time to recurrence of low back pain will be tested with the use of the Kaplan-Meier method and the logrank test. A multivariate Cox regression analysis will also be performed to adjust for the global program and all potential confounding variables.

The percentage of participants whose low back pain has become chronic in the two years following the program will be compared between the 2 study groups using a chi-squared test.

Qualitative thematic analysis of the content of the perceptions of the program users and of the health care professionals providing the program in terms of its organizational arrangements

This will be a qualitative thematic analysis of the content that aims to identify the elements of satisfaction or dissatisfaction and the degree of acceptability of the program for the various protagonists. These elements will be coded using the categories used initially in the interview guides (deductive approach). New coding categories will be generated through an inductive approach for the topics that do not correspond to the categories laid out in the interview guides. The coding will be carried out using Atlas.ti v5.2 qualitative analysis software
[21].

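### Delivery in session groups in the intervention arm only is not allowed for in the sample size or in the named tests

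*Protocol article*

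**What the plan says.** Under Education program, the protocol article describes an information session of about two hours for a group of eight. Under Training program, five weekly sessions of 90 minutes follow: "The patients meet in a group of eight to ten persons". Physiotherapists lead these "in a rotating manner in order to limit the therapist effect". Under Control group, controls receive only what they seek on their own initiative, so they have no session groups.

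Under Number of subjects required, the calculation starts "With a recurrence rate estimated at 45% for the general population, in order to observe a 25% reduction in recurrence rate" and concludes that "310 participants per group (a total of 620 participants) are required to achieve at 80% power with Type 1 error rate of 5" per cent. The only inflation is for loss ("A 5% increase in the number of participants is planned in order to take into account those lost to follow-up"), which brings the total to 650.

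The primary comparison is an ordinary chi-squared test, followed by logistic regression. Time to recurrence "will be tested with the use of the Kaplan-Meier method and the logrank test", followed by Cox regression. Results are to carry 95% confidence intervals. None of these sections mentions the session group. The Discussion weighs cluster randomization and contamination, but not correlation among people treated together.

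**The concern.** Participants who go through the same sessions with the same companions may come to have more similar outcomes than participants from different groups. At 310 per arm and 8 to 10 per group, there are about 31 to 39 such groups in the intervention arm and none in the control arm. Clustering in one arm makes that arm's proportion more variable than the binomial formula assumes, and every named test uses that formula or its equivalent.

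At stake are the width of the reported intervals, the meaning of the stated power and, in one setting, the 5% level. The plan already accepts that delivery can make outcomes alike, since it rotates physiotherapists for that reason. Rotation does not remove shared companions or a shared session history.

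**Working it through.** **Inputs from the protocol.** Control recurrence is 45%. A 25% relative reduction gives 0.45 × 0.75 = 33.75%, a difference d of 0.1125. There are 310 per arm, with two-sided alpha 0.05 ("All statistical tests were two sided p-value less than 0.05 regarded as significant") and 80% power. Group size m is 8 to 10.

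**Input assumed.** The ICC is not in the document. It is shown at 0, 0.01, 0.02, 0.05 and 0.10.

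**Reproducing the plan's figure.** The mean proportion is p̄ = (0.45 + 0.3375)/2 = 0.39375, so p̄(1−p̄) = 0.2387. The arm variances are 0.45 × 0.55 = 0.2475 and 0.3375 × 0.6625 = 0.2236.

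- n = [1.96·√(2 × 0.2387) + 0.8416·√(0.2475 + 0.2236)]² / 0.1125² = 295 per arm.
- With continuity correction, n = 313, close to the stated 310.
- Power at 310 per arm is 81.9% without the correction and 79.7% with it.

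The stated size is therefore a calculation for independent individuals.

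**Number of groups.** 310/10 = 31, and 310/8 = 38.75, or about 39.

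**Adding clustering in the intervention arm only.**

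- Design effect in that arm: DE = 1 + (m − 1) × ICC.
- Level of the ordinary test when group effects exist but average to zero: 2·[1 − Φ(1.96·√(2/(1 + DE)))].
- Power of a test that allows for the clustering: Φ{[d − 1.96·√(0.2387(1 + DE)/310)] / √((0.2475 + DE × 0.2236)/310)}. The continuity-corrected version replaces d by d − 1/310.

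**Worked case, m = 9, ICC 0.05.** DE = 1.40. The level is 2·[1 − Φ(1.96 × √(2/2.40))] = 2·[1 − Φ(1.789)] = 7.4%. The null standard error is √(0.2387 × 2.40/310) = 0.0430. The standard error under the alternative is √((0.2475 + 1.40 × 0.2236)/310) = 0.0425, against 0.0390 under independence. Power is Φ[(0.1125 − 1.96 × 0.0430)/0.0425] = 74.7%.

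**Range over m = 8 to 10.** CC means continuity correction.

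| ICC | DE | Level of ordinary test | Power, no CC | Power, CC | N per arm for 80%, CC |
|---|---|---|---|---|---|
| 0 | 1.00 | 5.0% | 81.9% | 79.7% | 313 |
| 0.01 | 1.07-1.09 | 5.4-5.5% | 80.3-80.6% | 77.9-78.3% | 323-326 |
| 0.02 | 1.14-1.18 | 5.8-6.1% | 78.6-79.3% | 76.2-77.0% | 333-339 |
| 0.05 | 1.35-1.45 | 7.1-7.7% | 73.8-75.6% | 71.3-73.1% | 364-378 |
| 0.10 | 1.70-1.90 | 9.2-10.4% | 66.5-69.6% | 64.0-67.1% | 415-444 |

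The intervention-arm standard error is understated by 3-4%, 6-8%, 14-17% and 23-28% at ICC 0.01, 0.02, 0.05 and 0.10.

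**The case against.** A reader might infer that the stated 5% and 80% simply fail. The document does not support that. It gives no ICC, and at zero nothing changes. At 0.01 and without continuity correction, power still exceeds 80%.

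A reader might also treat the groups as fixed. They are not strictly so. Table 1 invites absentees to make up sessions with another group, sessions 3 and 4 can replace each other, and physiotherapists rotate. The contact is one information session and five training sessions, and the continuing part is individual exercise at home. All of this may weaken a group effect. On the other side, Training program otherwise bars a participant from continuing after an absence, so membership is probably stable for most.

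It is tempting to count shared workplace and season as further one-arm clustering. Randomization is individual and stratified by occupational health service, so controls come from the same services over the same period, and those influences act largely on both arms. Only what arises in the session group itself counts here.

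On the level, groups form after individual randomization. If neither the program nor its group setting affects anyone, the ordinary chi-squared test keeps its 5%. This objection stands for the level. It does not rescue the intervals or the power, which concern a situation where the program has an effect that may differ between groups.

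Finally, variance modelling is often left to the analysis plan, which is not shown. That is fair for the model details. But this document itself fixes an individual-level chi-squared primary test and a stated power with no condition attached.

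**Conclusion.** The point holds as a conditional one. Delivery is grouped in one arm, and neither the sample size nor any named test allows for it. Given a positive within-group correlation, the intervention-arm standard error and the confidence intervals are too small, and power is below its value under independence. Error above 5% needs the further condition that group effects exist but average to zero.

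The size rests on an assumed ICC, equal groups of 8 to 10, 310 analysed per arm and stable membership. It is minor at 0.01, amounts to about 3 points of power at 0.02, and becomes material from about 0.05, where power is roughly 74-76% (71-73% with continuity correction). Nothing in the document shows which value applies. This should be corrected before analysis; it does not invalidate the design.

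**What to change.** Assign each intervention participant, including those who never attend, to the session group scheduled in the allocation letter described under Randomization. Treat each control as a group of one.

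For the primary outcome and time to recurrence, report the treatment effect from a partially nested model (a random effect for session group in the intervention arm only) or with a small-sample-corrected cluster-robust variance. For time to recurrence, use a robust-variance or shared-frailty Cox model. Do this at least as a prespecified sensitivity analysis beside the chi-squared and logrank tests, and report the ICC.

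Restate the 80% power as holding under independence, and give the figures at ICC 0.02 and 0.05.

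The cost is analysis-plan wording and modest programming, slightly wider intervals and a slightly lower stated power. No additional enrolment is needed. One check comes first: the document says the letter carried the session timetable and that attendance sheets are signed at every session, but not that a group identifier is kept. With make-up sessions, the sheets may show more than one group per person, so it must be confirmed that the scheduled group is recorded.
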